### Data collection and monitoring

Outcome measures are taken before first administering the test food (visit 1) and after 8 weeks, at the end of administration (visit 3), via laboratory tests. For the screening, AST, ALT, ALP, γ-GTP, total cholesterol, FBS, total bilirubin, BUN, creatinine, CRP, ESR, WBC, RBC, Hb, Hct, platelets, triglyceride, HDL, LDL, Na, K, and Cl are measured. At visit 1, NK cell activity, TNF-α, IFN-γ, IL-1β, IL-2, IL-6, IL-12, IgG1, IgG2, and IgM are also measured, and AST, ALT, ALP, γ-GTP, total cholesterol, FBS, total bilirubin, BUN, creatinine, CRP, ESR, WBC, RBC, Hb, Hct, platelets, triglyceride, HDL, LDL, Na, K, Cl, NK cell activity, TNF-α, IFN-γ, IL-1β, IL-2, IL-6, IL-12, IgG1, IgG2, and IgM are measured at visit 3. Personal information is collected during screening. The investigator processes the data, including personal information, under the clinical study protocol approved by the IRB. The subjects’ names remain confidential and the subjects are identified only according to their assigned randomized number. The principal investigator and sub-investigator secure the data, including personal information, in locked cabinets. Access to the data is restricted. All data are handed to storage manager after the clinical trial results have been reported, and the data is preserved for 3 years from the date of completion of the trial. When requested by monitors, inspection implementers, the IRB, or the Minister of Food and Drug Safety, the relevant documents are provided for access. The principal investigator requests the contract research organization (CRO) to monitor the study according to the plan and schedule. The CRO is independent from the sponsor and any competing interests. The CRO reviews the consent forms and evidence documentation and checked the capture of the main evidence data for quality control. If necessary, the CRO may request an investigator interview. Monitoring is conducted at the beginning of, during, and at the end of the trial by LAB to MEDI CRO (Seoul, Republic of Korea). During monitoring, research plans, case records, and annexed documents are reviewed to check whether they had been scientifically performed according to the plans approved by the IRB, and to ensure that the safety and rights of the research subjects are not infringed.

### Statistical analysis

Demographic data collected during screening will be tested using *t* tests (or Wilcoxon rank–sum tests) for continuous data. For categorical data, a chi-squared test (or Fisher’s exact test) will be performed. Effectiveness evaluation will be based on the results of the full analysis dataset. The per-protocol (PP) group will also be analyzed for reference. Statistical significance will be determined based on a significance level of 5%. If the difference between the two groups is normally distributed, an independent *t* test will be performed; if not, a Mann–Whitney *U* test will be performed. To test for differences before and after the treatment within a group, paired *t* tests will be used for normally distributed data; otherwise, Wilcoxon’s signed-rank tests will be used. The Shapiro–Wilk test will be performed to test the normality of continuous variables. When a difference between groups is observed, the drinking history variable will be considered for control variable, and additional covariate analysis will be performed. In the full dataset analysis, missing values will be replaced by the last observation carried forward. For the safety evaluation, the 95% confidence interval for each group will be determined by calculating the rate of occurrence of adverse reactions, and comparisons will be made between the groups. From the results of each laboratory test, continuous data such as vital signs will be compared with the baseline and analyzed using either a *t* test or a paired *t* test. If the assumption of normality is not satisfied, the Wilcoxon signed-rank test or the Wilcoxon rank–sum test will be performed. Categorical data will be analyzed using chi-squared tests and Fisher’s exact tests to determine whether there are differences between the groups in terms of the frequency and ratio of each category.

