### Sample size calculation

The necessary sample size is calculated using the NK cell activity results from the pilot study, in which this variable is used to evaluate efficacy. Calculations are performed using G*power 3.1.9.4, and the minimum number of subjects required to confirm statistical significance is determined to be 41 individuals per group. Accounting for a dropout rate of 15%, we aim to recruit a total of 98 people, with 49 for each group.

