### Outcome measures

The primary outcome is the amount of change in NK cell activity. NK cells play a key role in immune function against viruses and have recently been shown to play an important role in anticancer activity [8]. NK cell activity is measured to evaluate whether immune function increased as a result of the treatment. The secondary outcome is the amount of change in WBC in the peripheral blood and in the levels of TNF-α, IFN-γ, IL-1β, IL-2, IL-6, IL-12, IgG1, IgG2, and IgM. Proinflammatory cytokines such as TNF-α, IFN-γ, IL-1β, IL-2, IL-6, and IL-12 are factors that regulate the inflammatory responses of tissues [9]. Immunoglobulins such as IgG1, IgG2, and IgM are involved in virus neutralization and aggregation reactions. They also play a major role in immunity against influenza [10]. Changes in immune function can thus be confirmed by measuring changes in cytokines and immunoglobulins.

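### The primary NK comparison leaves out the baseline NK value already collected, and a normality test decides what is estimated; a prespecified baseline-adjusted analysis would usually be more precise

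*Protocol article*

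**What the plan says.** Under Outcome measures, "The primary outcome is the amount of change in NK cell activity". Under Data collection and monitoring, NK activity is measured once before treatment (visit 1) and once after eight weeks (visit 3).

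Under Statistical analysis, the between-group test is conditional: "If the difference between the two groups is normally distributed", it is an independent t test, and if not, a Mann–Whitney U test. The Shapiro–Wilk "test will be performed to test the normality of continuous variables". One covariate is named, and it is conditional too: "When a difference between groups is observed, the drinking history variable will be considered for control variable, and additional covariate analysis will be performed". Baseline NK activity is not named as a covariate.

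Under Sample size calculation, "the minimum number of subjects required to confirm statistical significance is determined to be 41 individuals per group", and the target is 49 per group after a 15% dropout allowance.

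**The concern.** Two features of the written rule weaken the primary result.

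- **Baseline is not used.** The visit 1 value enters only through subtraction, which fixes its coefficient at one. When the correlation between the two visits is below one, the coefficient that minimises the error variance is generally different, so precision is lost. A chance imbalance in baseline NK also feeds into the observed change through regression to the mean. The drinking-history analysis does not remedy this: it concerns another variable and is run only after a difference has been seen.
- **The data choose the estimand.** A t test addresses a difference in mean change, and a Mann–Whitney test addresses a shift in ranks. Which of them the trial reports is unknown until Shapiro–Wilk has been run on the outcome.

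With 41 evaluable participants per arm planned, power that could be had without extra participants or measurements is worth having.

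**Working it through.** **Inputs from the article.** 41 evaluable per group, 15% dropout, 49 per group, 1:1 allocation, 5% significance level, one baseline and one week-8 NK value.

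**Assumptions.** The article does not give the baseline-to-week-8 correlation ρ (range taken: 0.3 to 0.9), the power (80% taken), the sidedness (two-sided taken), or the effect size and SD. Equal variances at the two visits are assumed except where stated.

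**Step 1, the plan's own figure.** 41 / 0.85 = 48.2, rounded up to 49 per group and 98 in total. This reproduces. The 41 itself cannot be rebuilt from the article. At two-sided 5% it fits a standardized difference in change of d = 0.626 for 80% power (0.725 for 90%, 0.806 for 95%).

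**Step 2, variances.** With SD σ at both visits, the variance of the estimated group difference is proportional to

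- change score: 2σ²(1 − ρ)
- ANCOVA: σ²(1 − ρ²)

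The ratio of ANCOVA to change is (1 + ρ)/2, so the SE ratio is √((1 + ρ)/2). Estimating the slope multiplies the ANCOVA SE by about √(1 + 1/(N − 4)). With N = 82 this is √(1 + 1/78) = 1.006. Error degrees of freedom fall from 80 to 79.

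**Step 3, results** (power from the noncentral t with 79 df, d = 0.626 divided by the SE ratio):

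| ρ (assumed) | SE ratio, large sample | SE ratio with penalty | SE reduction | Power at 41 per arm, without / with penalty | n per arm for 80% |
|---|---|---|---|---|---|
| 0.3 | 0.806 | 0.811 | 19% | 93.5% / 93.2% | 28 |
| 0.5 | 0.866 | 0.872 | 13% | 89.9% / 89.5% | 32 |
| 0.7 | 0.922 | 0.928 | 7% | 86.0% / 85.5% | 36 |
| 0.9 | 0.975 | 0.981 | 2% | 82.0% / 81.5% | 40 |

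Simulation with normal errors (20,000 trials per setting, 41 per arm) gave ANCOVA power of 93.4%, 89.4%, 85.6% and 81.2%, against about 80% for the change-score t test. ANCOVA type I error was 4.5% to 5.1% over all settings.

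**Step 4, break-even.** Setting ((1 + ρ)/2)(1 + 1/78) = 1 gives ρ = 2 × 78/79 − 1 = 0.975. Only above that does the lost degree of freedom outweigh the gain.

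**Step 5, unequal variances.** The change-score variance minus the ANCOVA variance is proportional to (SD at baseline − ρ × SD at week 8)², which is never negative. In large samples adjustment therefore cannot lose to the t test on change.

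**Step 6, the normality switch.** Applying Shapiro–Wilk within each arm and then the chosen test (4,000 trials per setting) gave type I error between 4.4% and 5.7%. The switch does little harm to the error rate.

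**Step 7, skewed errors.** With lognormal errors (log-scale SD 0.8), power was:

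| ρ | Written two-branch rule | Linear ANCOVA | t test on change |
|---|---|---|---|
| 0.3 | 90% | 92% | 81% |
| 0.5 | 93% | 89% | 82% |
| 0.7 | 96% | 85% | 81% |
| 0.9 | 99% | 83% | 82% |

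Linear ANCOVA still beats the t branch, but the Mann–Whitney branch can beat linear ANCOVA. A separate lognormal simulation showed the same pattern (97% against 89% at ρ = 0.5, 99% against 87% at 0.7). A rank-based baseline-adjusted analysis did about as well as the written rule or better at those two correlations.

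**The case against.** The best defence is that nothing here is an error. A t test on change in a randomized trial is valid and unbiased over randomization, it matches the stated outcome, and its standard error already allows for chance baseline imbalance. The switch is prespecified and barely moves type I error. All of this stands, so the point concerns efficiency and a fixed estimand, not validity.

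A reader might infer more, in three ways that the documents do not support:

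- **That adjustment is free and always better.** It costs one degree of freedom, and the gain is only about 2% of the SE at ρ = 0.9. The power gain over the written rule depends on approximate normality. The article gives neither the correlation nor the distribution of NK activity.
- **That the switch biases the test or inflates false positives.** The simulated error rates do not show this.
- **That carrying the last observation forward will drive the switch.** A missing visit 3 NK value would become a zero change. Seven or eight such zeros per arm of 49 make Shapiro–Wilk reject in about 33% to 40% of simulated trials, against about 10% without them. That assumes testing within each arm and that every dropout lacks a visit 3 value yet stays in the full analysis set. The article states neither. It is also a missing-data question, separate from baseline adjustment.

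The power figures use 41 per arm, the planned evaluable number. The full analysis set could hold up to 49, which changes absolute power but hardly changes the SE ratios.

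It cannot be said that this belongs to an unseen analysis plan: the article itself states the test, the rule that selects it and the only covariate.

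**Conclusion.** The point holds as a recommendation that should be adopted. The written primary test is valid, but it leaves out a covariate that is already collected and lets a normality test choose between two estimands. Under approximate normality the loss is between about 2% and 19% of the standard error for ρ from 0.9 down to 0.3, or about 2 to 13 percentage points of power if the plan has 80% on change. Confidence in the direction under normality is high. The size depends on a correlation and a power that the article does not give. With strongly skewed errors the advantage of untransformed ANCOVA over the written rule can reverse, so the scale must be fixed in advance as part of the remedy.

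**What to change.** Replace the normality-gated choice with one named primary analysis: ANCOVA of week-8 NK activity on treatment group, with visit 1 NK activity as covariate, reporting the adjusted difference and its 95% CI.

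State the scale in advance, without looking at unblinded outcome data; the pilot NK results can inform it. For markers expected to be skewed, prespecify either a transformation (for example log) or a rank-based ANCOVA. Apply the same baseline-adjusted approach, on the prespecified scale, to each secondary marker.

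The cost is a wording change and one of 80 error degrees of freedom. It needs no extra participants, visits or blood samples.

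### Adjustment for drinking history waits for an undefined observed group difference, and the adjusted and unadjusted results are not ranked

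*Protocol article*

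**What the plan says.** All of this stands in the protocol article. Under Outcome measures: "The primary outcome is the amount of change in NK cell activity". Under Statistical analysis, the between-group comparison is unadjusted: "If the difference between the two groups is normally distributed, an independent *t* test will be performed; if not, a Mann–Whitney *U* test will be" (the quotation stops one word short of the sentence's end). The significance level is 5%; sidedness is not given.

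The same section then adds: "When a difference between groups is observed, the drinking history variable will be considered for control variable, and additional covariate analysis will be performed". Three features matter. The adjusted analysis has a condition. Using the covariate is itself only something to be considered. The analysis is described as additional to the comparison already named. No threshold for the observed difference is given, and no adjusted analysis without a condition is planned anywhere in the article.

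The section also plans significance tests of baseline characteristics: "Demographic data collected during screening will be tested using *t* tests (or Wilcoxon rank–sum tests) for continuous data". It does not link those tests to the choice of covariate. The randomization section describes 1:1 block allocation and names no stratification factor, so the design does not fix drinking history as a covariate either.

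**The concern.** Whether an adjusted treatment effect exists at all depends on what the data show, and the condition can be read in two ways.

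- **Outcome difference.** The adjusted model is fitted only after the unadjusted result is known. It can confirm or weaken a positive result, but it is never fitted where the unadjusted test misses an effect that adjustment would have found.
- **Baseline difference.** A significance test decides whether to adjust. In a randomised trial such a test measures chance, not prognostic importance, so an imbalance just short of the threshold goes uncorrected even if the covariate matters.

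The article gives no explicit order of precedence for the case where the two results conflict. The reading of the condition and the weight given to each result could therefore both be settled after the data are seen. At stake are some precision and a clear basis for the primary conclusion on NK cell activity.

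**Working it through.** **The plan's own figure.** Sample size calculation states that "the minimum number of subjects required to confirm statistical significance is determined to be 41 individuals per group", and then: "Accounting for a dropout rate of 15%, we aim to recruit a total of 98 people, with 49 for each group". Check: 41 / (1 − 0.15) = 48.2, rounded up to 49; 2 × 49 = 98. This reproduces. The 41 itself cannot be rebuilt, because effect size, SD and power are not stated. By the noncentral t distribution, 41 per group gives 80% power at two-sided 5% for a standardised effect d = 0.626. That d is used below as an assumption.

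**Inputs.** From the article: 41 or 49 per group, 1:1 allocation, 5% level. Assumed: two-sided testing, a binary drinking variable with 50% drinkers, correlation r between drinking and outcome of 0, 0.3 or 0.5, normal outcomes, and a trigger of p < 0.05. Each scenario has 40,000 simulated trials, comparing the unadjusted t test with a linear model that adds drinking history. The Mann–Whitney branch was not simulated.

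**Results with 41 per group:**

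| Quantity | r = 0 | r = 0.3 | r = 0.5 |
|---|---|---|---|
| Type I error, unadjusted | 4.9% | 5.1% | 5.0% |
| Type I error, always adjusted | 5.0% | 4.9% | 4.9% |
| Type I error, adjust only if drinking is imbalanced at p < 0.05 | 5.0% | 4.8% | 4.3% |
| Type I error, both results must be significant | 4.5% | 3.6% | 2.6% |
| Type I error, both always run and either may be claimed | 5.4% | 6.4% | 7.3% |
| Null trials: significant unadjusted results lost on adjustment | 8% | 30% | 48% |
| d = 0.626: power, unadjusted | 79.6% | 80.0% | 80.3% |
| d = 0.626: power, always adjusted | 79.0% | 82.9% | 89.7% |
| d = 0.626: only the adjusted model significant | 0.8% | 4.9% | 10.7% |

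**Outcome reading.** If the trigger is a significant unadjusted result, the adjusted model runs only when the trial is already positive. It cannot add a false positive, so error stays at the unadjusted 5%, or falls to 4.5–2.6% if both must be significant. The loss is on the other side. At d = 0.626 the model is never run in the 4.9% (r = 0.3) or 10.7% (r = 0.5) of trials where it alone is significant; with 49 per group the shares are 3.9% and 8.3%. Some trials are significant only without adjustment, so the net power gain from always adjusting is smaller: 82.9 − 80.0 = 2.9 points at r = 0.3 and 89.7 − 80.3 = 9.4 points at r = 0.5.

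**Baseline reading.** The trigger fires by chance in about 6% of trials. Overall error is 5.0–4.3%. Given a drinking imbalance of z standard errors that is left unadjusted, the null test statistic is shifted by r·z and has SD √(1 − r²). For z = 1.9, just under 1.96:

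- r = 0.2: shift 0.2 × 1.9 = 0.38, SD 0.980, conditional error 6.2%
- r = 0.3: shift 0.57, SD 0.954, conditional error 7.7%
- r = 0.5: shift 0.95, SD 0.866, conditional error 12.2%

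An absolute imbalance between 1.90 and 1.96 occurs in about 0.7% of randomisations.

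**Both models run, better one claimed.** Error is 6.4% and 7.3% at r = 0.3 and 0.5 with 41 per group, and 6.3% and 7.1% with 49. A separate run of 20,000 trials with 49 per group gave 6.1% at r = 0.2.

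**The case against.** The strongest reply is that the rule, as written, does little harm. A reader might infer that it inflates type I error to 6–7%, or even to 12%. The documents do not support that. The 6–7% needs both models run in every trial and a free choice between them, which the article does not describe. The 6.2–12.2% applies only to an imbalance chosen just below the cutoff, with an assumed correlation; averaged over all imbalances, error is at or below about 5%, and over randomisation the unadjusted estimate is unbiased. This part of the reply stands in full.

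A reader might also infer that the adjusted result replaces the unadjusted one. The word additional points the other way: the unadjusted comparison is named first and the covariate analysis supplements it. Nor would most null trials have two p-values, since a p < 0.05 trigger of either kind fires in only about 5–6% of them. That the demographic tests select the covariate is likewise only one possible reading; the article neither says so nor lists drinking history among the demographic data. Finally, one covariate is named in advance, so there is no open pool to search.

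Two things remain. The hierarchy is implied, not stated, and with r = 0.3–0.5 some 30–48% of significant unadjusted results in null trials are lost on adjustment, so conflict would not be rare. And this is not detail left to an analysis plan or full protocol that is not shown: the article itself states a rule that depends on the data, and those documents could remove it only by departing from the published sentence.

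**Conclusion.** The point holds at moderate severity. The article ties its only adjusted analysis to an observed difference without saying of what kind, and gives no explicit precedence if the two results conflict. The main cost is lost information: under the outcome reading, about 5–11% of trials would never run the one model that detects the effect (41 per group, d = 0.626, r = 0.3–0.5). Under the baseline reading, near-threshold prognostic imbalance stays uncorrected. Strictly followed, the rule keeps overall type I error at or below about 5%; the room for about 6–7% opens only if both models are run and the more favourable may be claimed (r = 0.2–0.5). All these sizes rest on assumed prevalence, correlation and, for power, effect size, none of which the article gives. If drinking history is unrelated to change in NK cell activity, there is almost no loss: 0.8% of trials.

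**What to change.** Delete the condition and choose one of two wordings before unblinding.

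1. Make the primary analysis one pre-specified ANCOVA of NK cell activity containing drinking history and baseline NK cell activity, fitted whatever the observed balance or result.
2. Keep drinking history out of the primary model and run the adjusted model as one fixed sensitivity analysis in every case, labelled supportive, with the primary result deciding the conclusion.

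Under either wording, state that baseline significance tests play no part in choosing covariates. Including baseline NK cell activity is a further improvement and is not needed to cure the condition itself; its effect was not simulated.

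The cost is a rewritten sentence and about one degree of freedom per covariate (two in the first option if drinking history is binary). The sample size of 98 is unchanged. Always adjusting for drinking history kept simulated error at 4.9–5.0%, with power of 79%, 83% and 90% at r = 0, 0.3 and 0.5, against about 80% unadjusted.

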## Methods

### Study design

This is a prospective, double-blind, single-center, randomized, controlled clinical trial designed to demonstrate the effects of PL extract on immune function. Recruitment starts in October 2020 and the trial ends in March 2021. Subjects are recruited via placards on outdoor billboards and banners in Daejeon University Cheonan Korean Medicine Hospital. All subjects receive written explanations and informed consent forms for the clinical trial protocol from a Korean medical doctor (KMD). The KMD also comprehensively explains the study to the recruited subjects, receives informed consent from them, and selects participants in the study based on detailed screening.

The study planned to recruit 98 subjects who will be randomly assigned in a 1:1 ratio to either the experimental group (PL 1000 mg) or the control group (placebo). The subjects take one 500 mg capsule twice daily for eight weeks, and this capsule contains either PL or dextrin, depending on the group they had been assigned to.

The variables we evaluated are NK cell activity, TNF-α, IFN-γ, IL-1β, IL-2, IL-6, IL-12, IgG1, IgG2, and IgM. Blood samples are taken for this laboratory test on the first day of participation, before the subjects has begun ingesting the test food, and 8 weeks later, at the end of the trial. The subjects visit the clinic three times and the clinical trial span a total of eight weeks (Table 1, Fig. 1).

**Table 1 Tab1:** Clinical trial process for the *Phellinus linteus* extract clinical trial protocol

Section	Screening	Visit 1 (baseline visit)	Visit 2 (during trial)	Visit 3 (trial end)
	(− 2 weeks to 0 days)	(0 days)	(4 weeks ± 5 days)	(8 weeks ± 5 days)
Prepare a written consent form	√			
Evaluate inclusion/exclusion criteria	√			
Examine subject information	√			
Assign screening number	√			
Assign random numbers to subjects		√		
Investigate medical history and medication history	√	√		
Conduct physical examination	√	√	√	√
Assess vital signs	√	√	√	√
Conduct clinical laboratory blood test	√	√		√
Conduct pregnancy test	√			
Observe upper respiratory tract infection symptoms		√	√	√
Distribute experimental/control foods		√	√	
Measure effectiveness-evaluation variables		√		√
Check adverse events			√	√
Identify concomitant drugs			√	√
Check compliance			√	√
Confirm cancelation and withdrawal criteria		√	√	√

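### Efficacy markers are measured only at baseline and week 8, so LOCF scores any participant kept in the full analysis set without a week-8 value as exactly zero change

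*Protocol article*

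**What the plan says.** All places are in the Methods of the protocol article.

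- **Outcome measures:** "The primary outcome is the amount of change in NK cell activity". The secondary outcomes are changes in WBC, immunoglobulins and cytokines.
- **Timing, in the section on data collection:** the article gives two time points, "Outcome measures are taken before first administering the test food (visit 1) and after 8 weeks, at the end of administration (visit 3". Study design agrees that blood is drawn "before the subjects has begun ingesting the test food, and 8 weeks later, at the end of the trial". Table 1 ticks the effectiveness variables at visits 1 and 3 and leaves visit 2 (week 4) blank.
- **Statistical analysis, main set:** "Effectiveness evaluation will be based on the results of the full analysis dataset". The supporting analysis is per-protocol: "The per-protocol (PP) group will also be analyzed for reference".
- **Statistical analysis, missing data:** "In the full dataset analysis, missing values will be replaced by the last observation carried forward".
- **Sample size calculation:** "Accounting for a dropout rate of 15%, we aim to recruit a total of 98 people, with 49 for each group", starting from 41 per group.
- **Withdrawal and dropout:** participants who leave have a laboratory test. Its stated purpose is safety, and NK cell activity is not named.

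**The concern.** LOCF needs a post-treatment observation to carry. Here there is none between baseline and the endpoint, so for NK cell activity, the cytokines and the immunoglobulins the rule is baseline carried forward. WBC may also have a screening value, but that too precedes treatment.

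The imputed change is baseline minus baseline, which is zero whatever happened to the participant. These zeros enter the analysis that carries the efficacy conclusion. They pull each arm's mean change towards zero in proportion to that arm's dropout. The between-arm estimate is then diluted. If the arms lose different proportions while both change over time, a difference appears that treatment did not cause.

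The article states the rule outright, so this is a choice made in the text and not a detail left to an analysis plan.

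**Working it through.** **Inputs from the article.** 41 evaluable per group, 15% dropout, 49 per group, significance level 5%, two measurement times.

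**Inputs assumed.** The article gives no effect size, SD, power or sidedness. I take the SD of change as 1 and read 41 per group as two-sided 5% with 80% power. Solving the noncentral t power equation at n = 41 gives d = 0.626. Over one- or two-sided tests and 80% or 90% power, d ranges from 0.55 to 0.72. Unequal dropout and drift (a change common to both arms) are also assumptions.

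**The plan's own figure.** 41 / (1 − 0.15) = 48.2, rounded up to 49 per group and 98 in total. This reproduces.

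**How many zeros.** 49 × 0.15 = 7.35, so about 7 to 8 per group, or about 15 of 98 (98 × 0.15 = 14.7).

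**Formulas.** For an arm with mean change μ, SD 1 and random dropout p, all dropouts being set to zero:
- mean = (1 − p)μ
- variance = (1 − p) + p(1 − p)μ²
- SE of the difference = √[(variance PL + variance placebo) / 49]

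**Case 1: 15% dropout in both arms, no drift, true effect 0.626.**
- Estimate: 0.85 × 0.626 = 0.532, which is 15% too small. The bias is 0.532 − 0.626 = −0.094.
- Variances: PL 0.85 + 0.1275 × 0.392 = 0.900; placebo 0.85. SE = √(1.750 / 49) = 0.189.
- Bias / SE = −0.094 / 0.189 = −0.50. Simulated coverage of the true effect is 92%.
- Simulated power is 79.8%, against 80.4% for observed cases.
- With no true effect, simulated type I error stays near 5% for a drift of 0, 0.5 or 1 SD.
- With a drift of 0.5 SD and the true effect present, power is about 77%.

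**Case 2: no true effect, unequal dropout, common drift m.** The bias is m × (placebo dropout − PL dropout).

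| Dropout PL vs placebo | Drift (SD) | Bias (SD) | Simulated type I error |
|---|---|---|---|
| 25% vs 5% | 0 | 0 | about 5% |
| 20% vs 10% | 0.5 | 0.5 × (−0.10) = −0.05 | about 6% |
| 20% vs 10% | 1.0 | 1.0 × (−0.10) = −0.10 | about 8% |
| 25% vs 5% | 0.5 | 0.5 × (−0.20) = −0.10 | about 8% |
| 25% vs 5% | 1.0 | 1.0 × (−0.20) = −0.20 | 17% |

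Analysing observed cases keeps type I error at 5% when dropout is random within arm. The sign of the bias follows the drift and the arm that loses more. Upward drift with heavier loss on PL counts against PL; reversing either one favours PL.

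**Choice of test.** The plan uses Shapiro–Wilk to choose between the t test and Mann–Whitney. Eight exact zeros among 49 otherwise normal values raise Shapiro–Wilk rejection from about 5% to 19% (mean change 0) or 27% (mean change 0.626). The imputation can therefore also influence which test is used.

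The simulations used 40,000 runs per scenario and a pooled t test; the Shapiro–Wilk check used 4,000.

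**The case against.** The best defence is that, under the dropout the article itself plans for, the primary test is sound. With 15% lost from both arms, type I error stays near 5%, power barely moves when there is no drift, and the dilution runs towards no effect. That stands, and it limits the severity.

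A reader might draw four stronger conclusions that the documents do not support:

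- **That every dropout is scored as zero.** The article does not define the full analysis set. If it required a post-baseline efficacy value, these participants would leave it and LOCF would have nothing to fill for NK cell activity. An exit sample that happened to include NK activity would also supply a value, although the exit test is described as a safety test only.
- **That the zeros make the standard error too small.** They do not. In Case 1 the mean reported SE (0.188) matches the estimator's actual spread (0.189), and the interval covers the estimator's own mean 95% of the time. Coverage of the true effect falls because the estimate is biased.
- **That type I error is inflated in this trial.** That needs unequal dropout and drift together, and the article gives figures for neither. Both are plausible: exits for adverse reactions or for drugs affecting the efficacy variables could differ by arm, and the trial runs from October to March. They remain assumptions.
- **That inflating 41 to 49 for losses conflicts with imputing those losses.** It does not. Allowing for dropout in recruitment is ordinary and contradicts nothing in the analysis.

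It can also be said that an analysis of observed values relies on missing-at-random, which the listed exit reasons make doubtful. That is fair, and it is why the fix includes a sensitivity analysis.

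**Conclusion.** The point holds for participants kept in the full analysis set without a week-8 value: the stated rule scores them as zero change on the primary outcome and on the cytokine and immunoglobulin outcomes. At the planned 15% dropout the consequence is an estimate about 15% too small and roughly 92% coverage of the true effect, with the test itself essentially intact. This rests on random dropout, normally distributed changes and the assumed effect of 0.626 SD; the proportional dilution itself does not depend on that effect size. A biased test, in either direction, arises only under the assumed combination of unequal dropout and drift, with type I error from about 6% to 17% across the scenarios shown. The rule should be changed, but it is not a fatal flaw.

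**What to change.** Replace the LOCF sentence in Statistical analysis with one of these as the primary analysis:

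- a baseline-adjusted analysis (ANCOVA) of week-8 NK cell activity in all randomised participants who have a week-8 value; or
- multiple imputation by arm, using the baseline value.

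Add a sensitivity analysis that departs from missing-at-random, for example delta-adjusted imputation. Baseline carried forward may be kept, but only as a sensitivity analysis and under that name. Define the full analysis set so that it is clear who is in it without a week-8 value. Apply the same rule to the secondary markers.

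The cost is a few sentences and a little programming. The analysed number falls or the intervals widen slightly, which the target of 41 evaluable per group already allows for. No further participants are needed.
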